**Frailty**		
Tilburg Frail Indicator (TFI)	Questionnaire	15 items
**Quality of life**		
Short Form 20 (SF-20)	Questionnaire	20 items
EuroQol (EQ-6D)	Questionnaire	6 items
Visual Analogue Scale (VAS)	Questionnaire	1 item
Social Production Function Instrument for Level of wellbeing (SPF-IL)	Questionnaire	15 items

**Secondary outcomes elderly**	**Instruments**	**Items**

**Health outcomes, functioning and abilities**		
Cognitive functioning	Questionnaire	6 items
Katz Index of Independence in Activities of Daily Living (ADL)	Questionnaire	15 items
Self Management Ability Scale Short version (SMAS-S)	Questionnaire	18 items
**Health behavior**		
Smoking behavior	Questionnaire	3 items
Physical Activity	Questionnaire	1 item
**Health care utilization**		
Health care utilization	Questionnaire	18 items
**Neighborhood experiences**		
Social cohesion and belonging	Questionnaire	15 items
Neighborhood quality index	Questionnaire	15 items
**Social resources**		
Social support index	Questionnaire	20 items
Social connection index	Questionnaire	5 items
Social support of partner/children/family and friends/neighbors	Questionnaire	6 items
Social capital	Questionnaire	9 items
Social participation	Questionnaire	2 items

**Outcomes caregivers**		

**Quality of life**		
Short Form 20 (SF-20)	Questionnaire	20 items
CarerQoL-7D	Questionnaire	7 items
CarerQol-VAS	Questionnaire	1 item
Social Production Function Instrument for Level of wellbeing (SPF-IL)	Questionnaire	15 items
**Health outcomes**		
Katz Index of Independence in Activities of Daily Living (ADL)	Questionnaire	15 items
**Caregiving experiences**		
Activity restriction scale	Questionnaire	10 items
Caregiver Strain Index (CSI+)	Questionnaire	18 items
Self-Rated Burden	Questionnaire	1 items
**Health care utilization**		
Health care utilization	Questionnaire	14 items
**Social resources**		
Social support of partner/children/family and friends	Questionnaire	6 items

**Process outcomes**		

Partnership Self-Assessment Tool Short version (PSAT-S)	Questionnaire	24 items
Relational Coordination Survey	Questionnaire	7 items
Intervention and other direct costs	Data registration	

#### ii. Effects

Assessment of effectiveness will be in terms of reaching the frail elderly, improving their self-management abilities and well-being, and improving the well-being of their informal carers. Demographic data and outcome indicators - well-being, quality of life, self-management abilities, cognitive functioning, social networks, social cohesion, sense of community in the neighbourhood - will be captured with specific instruments (table 1).

#### Instruments elderly

##### Frailty

The Tilburg Frailty Indicator (TFI) will be used to measure frailty. The results regarding the TFI's validity provide strong evidence for an integral definition of frailty consisting of physical, psychological, and social domains [12].

##### Quality of life and well-being

The Dutch version of the SF-20 is administered to the frail elderly. It aims to score 6 sub-dimensions such as physical functioning, social functioning and experienced health [17,18]. The SF-20 was chosen over the SF-36 because it is shorter and because many questions are included in the MDS. The EuroQol (EQ6D) and Visual Analogue Scale (VAS-scale) - part of the MDS - are administered to measure quality of life among the elderly and their informal caregivers. They will also be used to calculate cost-utilities of health care [19].

##### Well-being

The Social Production Function Instrument for the Level of wellbeing scale (SPF-IL) is used to measure the universal goals needed to be realized by individuals in order to enhance their well-being [20]. Social production function (SPF) theory asserts that the universal goals affection, behavioural confirmation, status, comfort and stimulation are the relevant dimensions of subjective well-being. Examples of questions are: 'do you feel that people really love you' and 'are you known for the things you have accomplished'.

##### Self-reported cognitive function

The MOS cognitive function scale will serve as the self-report measure of cognitive function. This scale contains six Likert-type items on memory, reasoning and thinking. The responses to individual questions are summed and the score is then converted to a 0-100 point scale, with 100 indicating the most favorable functioning [21,22]. Examples of items are: 'How much of the time during the past month did you have difficulty reasoning and solving problems, for example making plans, making decisions or learning new things' and 'How much of the time during the past month did you have trouble keeping your attention on any activity for long'.

##### Physical functioning

The Katz-15 index of activities of daily living measures function over time by means of statements on several domains such as bathing, dressing, toileting, transferring, continence and feeding [23]. Example: 'Moves in and out of bed or chair unassisted. Mechanical transferring aides are acceptable' or 'Needs help in moving from bed to chair or requires a complete transfer'.

##### Self-management

The SMAS-S (Self Management Ability Scale-Short version) measures a person's ability to manage his/her own general daily life activities in the past months. It contains 18 items on several self-management abilities [24,25]. Examples are: 'How often do you take the initiative to keep yourself busy?' and 'Are you capable of taking good care of yourself?'

##### Social cohesion & belonging

The neighborhood cohesion scale consists of 15 items on a person's contribution to the social cohesion in the neighborhood [26]. Examples are: 'I would be willing to work together with others on something to improve my neighborhood' and 'I regularly stop and talk with people in my neighborhood'.

##### Neighborhood quality

The Neighborhood Quality Index will be used to capture residents' perceptions of neighborhood quality [27]. Examples are: 'participating in activities together' and 'feeling safe in this neighborhood'.

##### Social support

The social support index will be used to assess levels of social support. This survey was designed to be comprehensive in terms of recent thinking about the various dimensions of social support. Multitrait scaling analyses supported the dimensionality of four functional support scales (emotional/informational, tangible, affectionate, and positive social interaction) and the construction of an overall functional social support index [28].

##### Social connections

The social connections index will be used to assess the level of social connections. This index contains five questions regarding social connections and has shown to be a predictive tool of mortality [29].

##### Social support of spouse, children, friends and relatives, and neighbors

This instruments assesses emotional support, instrumental support and negative aspects of relationships. Example of emotional support is 'how often does/do your [spouse/children/friends and relatives/neighbors] make you feel loved and cared for?" Example of instrumental support is 'how often does/do your [spouse/children/friends and relatives/neighbors] give you advice or information about medical, financial, or family problems?" Negative aspects of relationships were measured by two items that assessed the frequency with which participants' spouses, children, friends and relatives, or neighbors 'made too many demands' or 'were critical' [30].

##### Social capital

The Short Social Capital Assessment Tool (SASCAT) serves to assess social capital. The tool could also be used to measure ecological social capital by administering it to a representative sample of a community and aggregating their responses [31]. Examples of items are: 'in the last 12 months, did you receive from the group any emotional help, economic help, or assistance in helping you know or do things' and 'in general, can the majority of people in this community be trusted'.

##### Social participation

Following the study of Guillen and colleagues [32] we will measure social participation with the following questions: 'compared to other people of your age, how often would you say you take part in social activities' and 'how often do you meet socially with friends, relatives or neighbors'.

#### Instruments caregivers

##### Quality of life

In addition to the instruments also used with the elderly, the carer quality of life questionnaire (Carer QoL-7D) measures quality of life of informal carers and is part of the MDS [33,34].

##### Activity restriction

Burden of care for the carer is measured using the Activity Restriction Scale (ARS) [35]. Carers are asked to indicate the extent to which nine areas of normal activity (e.g., doing household chores, going shopping, visiting friends, participating in sports and recreation, maintaining friendships) are restricted by their caregiving responsibilities.

##### Self-rated burden and strain

Subjective burden of care is measured with the Self Rated Burden Scale (SRBS) and Caregiver Strain Index or CSI [36,37]. Examples of questions are: 'there have been family adjustments (e.g. helping has disrupted my routine; there is no privacy)' and 'there have been changes in personal plans (e.g. I had to turn down a job; I could not go on vacation)'.

#### iii. Costs

A cost-effectiveness evaluation will be performed to determine whether INA is a cost-effective method to support the frail, independently-living elderly. We will assess the additional (health care) costs involved in INA and the costs per quality-adjusted life years (QALY) gained in the elderly and their informal caregivers. INA costs may be higher than expected because extra care and support are offered and more people could avail themselves of the services, or they may be lower than expected because specific groups of elderly and their informal caregivers will earlier and more purposefully avail themselves of the services and receive better support from their networks, preventing or delaying serious (health) problems. Delaying or preventing admission to a nursing home, for example, lowers costs and often appeals to the elderly and informal caregivers.

Health care utilization and given support will be quantified via questionnaires and additional sources where possible (Client Monitoring System, local and national monitors). Multiplying these volumes by integral cost prices will yield total costs of care and support. For this purpose we will use the guideline of the Dutch Health Care Insurance Board (CVZ) [38]. INA costs are estimated via time registrations on professionals' activity levels. Different types of activity (such as contact with the elderly and team meetings), professional disciplines, and corresponding tariffs will be taken into account. Assessment costs will be included in the total costs for the intervention group only and not the control group, because the costs are incurred only within the INA framework. Finally, costs per centre will be calculated (e.g., costs of the interventions, welfare, health care, community workers), providing insight for all participating organizations as to the investments that will be needed to continue INA after the study phase.

The cost-effectiveness evaluation will be on the basis of the costs and the registered effects described above. The primary analysis is a regular cost-utility analysis with differences between the intervention and control groups in costs and well-being (QALY) during a 12-month follow-up as outcome, allowing us to compare findings with other studies.

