#### II. Controlled pre-post measurement (effect evaluation)

The independently-living elderly (70+) in the first two districts whose TFI-score is ≥ 5 [12] will serve as the experimental group and will be recruited by community workers. On the basis of TFI-score, age, and gender, they will be matched with the elderly recruited from comparable districts in Rotterdam as a control group. In total we expect to include 370 elderly (247 in the experimental group; 123 in the control group). All will be interviewed at home by experienced interviewers at three time-points: T0, T1 (6 months after inclusion), and T2 (12 months after inclusion). On average the interviews will take 60 minutes.

Informal caregivers will be interviewed twice by telephone for about 15 minutes each. They will be identified on the basis of the definition provided in the National Care for the Elderly Programme: those who provide structured care voluntarily and for free to people in their family, household, or social network with physical, mental or psychological disabilities. It involves providing more care than usual in personal relationship and consists of tasks that healthy people could normally do themselves.

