#### i. Process

The process evaluation study will find whether INA contributes to (a) continuous, demand-driven, coordinated care and support for independently-living frail elderly, and (b) reinforcing the welfare, health care, informal care and community networks in their neighbourhoods. We will describe INA in Rotterdam, how the various networks are reinforced, what they do, and how they cooperate to improve the self-management abilities and well-being of frail elderly. Process indicators will be registered continually during 12 months. Data such as descriptions of client visits, assessment outcomes, action goals, and agreements will be captured by a computerized Client Monitoring System and registration forms. An evaluation of the process indicators and data about contacts with professionals is expected to reveal any INA effects.

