### Weaknesses

In our study, health care utilization is mainly derived from questionnaires administered to the frail elderly and their informal caregivers instead of using direct and perhaps more accurate information from health care companies. Unfortunately, there is a long delay in declaration and registration of health care costs, which hampers the timely delivery of the information needed for the cost-effectiveness evaluation. Moreover, extracting information from the database of the healthcare insurance companies requires obtaining informed consent to collect the additional data in addition to written informed consent to participate, perhaps decreasing participation. Another drawback in using questionnaires might be the recall bias for health care utilization over the past three to six months, but the questionnaires will be administered by means of face-to-face interviews with the frail elderly, giving the interviewer opportunity to ask for clarification. And while we are not able to randomize the frail elderly in the intervention and control groups; we will match the two groups.

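### Care volumes may be supplemented from the Client Monitoring System, described only for INA, which puts the between-group cost difference at risk of unequal ascertainment or double counting

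*Protocol article*

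**What the plan says.** The costs section (iii. Costs) sets the source rule for care use and support: "Health care utilization and given support will be quantified via questionnaires and additional sources where possible (Client Monitoring System, local and national monitors". These volumes are then priced: "Multiplying these volumes by integral cost prices will yield total costs of care and support". The cost of the programme itself has a separate source: "INA costs are estimated via time registrations on professionals' activity levels". One item is explicitly assigned to a single group: "Assessment costs will be included in the total costs for the intervention group only and not the control group". The primary economic analysis in the same section is a cost-utility analysis of the between-group difference in costs and QALYs over 12 months.

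The Client Monitoring System is described in the process section (i. Process): "Data such as descriptions of client visits, assessment outcomes, action goals, and agreements will be captured by a computerized Client Monitoring System and registration forms". That section concerns INA: "The process evaluation study will find whether INA contributes to (a) continuous, demand-driven, coordinated care and support for independently-living frail elderly".

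On controls, the section on the controlled pre-post measurement says of the INA participants that "they will be matched with the elderly recruited from comparable districts in Rotterdam as a control group". No monitoring system or similar record is described for those districts.

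The Weaknesses section says that utilization comes mainly from questionnaires, and adds: "Another drawback in using questionnaires might be the recall bias for health care utilization over the past three to six months". It also notes that face-to-face interviewing lets the interviewer ask for clarification.

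**The concern.** A cost difference is interpretable when both groups' volumes are measured in the same way. Here the test for adding a source is whether it is possible to do so, and for the Client Monitoring System that appears to depend on the group. Volume that the system adds under care use and support can be of two kinds:

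- **Ordinary care or support**, which controls also use. It would then be recorded from two sources in the INA group and from one in controls.
- **INA contacts**, such as community-worker visits. These are real costs of INA, but the time registrations already cost professionals' contact with participants, so the same visit could enter twice.

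Both routes raise the recorded cost of the INA group. A larger sample does not remove such an error, and matching on TFI score, age and gender does not address it. At stake is the cost side of the cost per QALY, on which the article's second research question turns.

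**Working it through.** **1. No plan figure to reproduce.** The article gives no mean cost, spread, under-reporting rate or coverage of the Client Monitoring System. The check is a reading of the passages, followed by an illustration on assumed values.

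**2. The passages side by side.**

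| Element | INA group | Control group |
|---|---|---|
| Home interviews at T0, T1 and T2 | Yes | Yes |
| Client Monitoring System | Yes (i. Process) | None described |
| Local and national monitors | Coverage not stated | Coverage not stated |
| Time registrations for programme cost | Yes (iii. Costs) | Not applicable |

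The main source is symmetric and one named additional source is not. No passage requires the same sources in both groups, and none says that a contact found in both the system and the time registrations is counted once.

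**3. Unequal ascertainment.** Assumptions: true mean volume is 100 units in both groups, the questionnaire captures a share q of it in both, and the system recovers a share r of the missed volume in the INA group only.

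- Recorded INA volume = 100 × [q + (1 − q) × r]
- Recorded control volume = 100 × q
- False difference = 100 × (1 − q) × r
- Relative to recorded control volume = (1 − q) × r / q

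| q | r = 0 | r = 0.25 | r = 0.5 | r = 1.0 |
|---|---|---|---|---|
| 1.0 | 0 | 0 | 0 | 0 |
| 0.9 | 0 | 2.5 (2.8%) | 5.0 (5.6%) | 10.0 (11.1%) |
| 0.8 | 0 | 5.0 (6.3%) | 10.0 (12.5%) | 20.0 (25.0%) |
| 0.7 | 0 | 7.5 (10.7%) | 15.0 (21.4%) | 30.0 (42.9%) |

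At equal unit prices, the same percentages apply to cost.

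**4. Effect on a real saving.** Let true INA use be 90 against 100 in controls, with q = 0.8.

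- Same source in both groups (r = 0): 90 × 0.8 − 100 × 0.8 = 72 − 80 = −8.
- System added in INA only, r = 0.5: 90 × (0.8 + 0.2 × 0.5) − 80 = 81 − 80 = +1.

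On these assumptions a true saving of 10 units appears as an excess of 1.

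**5. Double counting.** Let C be the cost per INA participant of contacts already covered by time registrations, and d the share of them entered again as support. The INA group's cost is overstated by d × C: nothing if d = 0, the full contact cost if d = 1. The article gives neither C nor d. This route needs no recall error.

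**6. After the fix.** With r equal in both groups (or zero) and d = 0, equal true use gives a false difference of 0. Equal under-reporting still shrinks a true difference (−8 instead of −10 in step 4), but it does not create one.

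**The case against.** A reader might infer that the plan prescribes a top-up, that forgotten contacts are therefore recovered in INA participants only, and that the cost difference is biased by some definite percentage or euro amount. The documents do not support that, for these reasons:

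- The costs section does not say how sources are combined. They might be added, used for cross-checking, or used for items that the questionnaire lacks.
- What the process section lists is mostly INA activity. It does not name general practice, hospital, home care or nursing home use.
- INA visits and assessments arise only under INA. Counting them once, in that group alone, is correct costing.
- That controls are absent from the system is a strong inference from where it is described and where controls are recruited. It is not stated.
- Utilization comes mainly from questionnaires, given to both groups in home interviews where answers can be clarified.
- Recall bias is mentioned as a possibility, and it need not mean under-reporting. Whether the questionnaire asks about community workers is not shown.
- Item-level counting rules may sit in a fuller document.

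Most of this stands. It limits the certainty and size of the problem and rules out a euro figure. It does not remove the point, which concerns a rule that the article does state. Under that rule, volume from the system is either ordinary care seen in one group only or INA contact that the time registrations already cost. No passage resolves either case. The planned sensitivity analyses of major assumptions do not name data source and would not correct the base case.

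**Conclusion.** The point holds as a risk, not as a demonstrated bias. The costing rule allows a source described only for INA to feed the volumes behind the primary cost difference, without requiring equal sources or single counting of INA contacts. The likely direction is against INA. It rests on three assumptions: controls have no record in the system, questionnaires tend to miss use, and the system adds volume and does not merely replace or check it. For double counting, only the first and last of these matter, together with overlap with the time registrations.

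The size is unknown. The illustration runs from nil, when the questionnaire is complete or the system recovers nothing, to large enough to reverse a true 10-unit saving. Nil or small is plausible given the dominant role of the questionnaire. This is a cheap improvement to the plan.

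**What to change.** In the costs section, state that:

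1. The base-case between-group cost difference uses care and support volumes from sources available equally in both groups: the same questionnaire with the same recall period, and local or national monitors only where they cover both groups.
2. The Client Monitoring System and the time registrations are used only to cost the INA programme, and each INA contact is counted once. Where the questionnaire identifies INA contacts, they are removed from its volumes.
3. A version with volumes supplemented from the Client Monitoring System is reported as a sensitivity analysis.

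The cost is a few sentences, and items 1 and 3 need no further data collection. There are two drawbacks. Some support recorded only in the Client Monitoring System stays out of the base case. Removing INA contacts from questionnaire volumes is possible only if the questionnaire identifies them, which the article does not show.

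### The primary cost-utility comparison names no adjustment for T0 utility or T0 care use, although the groups are not randomised and are matched only on TFI, age and gender

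*Protocol article*

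**What the plan says.** All places are in the protocol article.

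- **Costs (section iii).** "The primary analysis is a regular cost-utility analysis", and its outcome is "differences between the intervention and control groups in costs and well-being (QALY) during a 12-month follow-up as outcome". No covariate or baseline correction is mentioned. The same section says that QALYs gained are counted in the elderly and in their informal caregivers.
- **Controlled pre-post measurement (section II).** The elderly in the first two districts "will serve as the experimental group and will be recruited by community workers". For the control group, "On the basis of TFI-score, age, and gender, they will be matched with the elderly recruited from comparable districts". The elderly are interviewed at inclusion, 6 months and 12 months.
- **Quality of life and well-being.** Of the EQ-6D and VAS: "They will also be used to calculate cost-utilities of health care".
- **Weaknesses.** "And while we are not able to randomize the frail elderly in the intervention and control groups; we will match the two groups".
- **Data analysis.** The elderly give data at T0, T1 and T2, and caregivers at T0 and T2 only. For the outcomes of the process and (cost-)effectiveness evaluations, the section lists multivariate analysis (per time point and longitudinal) and sensitivity analyses, without naming covariates.

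**The concern.** In a randomised trial, a baseline utility difference is chance, and leaving it in the QALY comparison mostly costs precision. Here the two groups live in different districts. The experimental group is found by community workers, so T0 utility and prior care use may differ systematically. Neither is a matching variable. Matching is also done at inclusion, while the Sample size section expects about 27% loss by T2, so any balance achieved need not survive in those analysed.

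Utility at T0 is normally part of a 12-month QALY. A T0 gap therefore enters the outcome directly, and again to the extent that utility persists to T1 and T2. Costs are exposed in a milder way. Prior use is not part of follow-up cost, but heavy users tend to remain heavy users.

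The second central research question is answered by the cost per QALY, which the Costs section wants to compare with other studies. A QALY difference that partly reflects who was recruited could change the size or sign of that ratio.

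**Working it through.** **Plan's own figure.** The article states no QALY or utility figure, so there is none to reproduce. From the plan come the measurement times (0, 6 and 12 months for the elderly; T0 and T2 for caregivers) and the expected final sample of 180 and 90. The T0 utility gap d, the carry-over slope b and the utility SD are assumptions. So is the area-under-the-curve construction, which is usual but not stated.

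**Step 1: weight of T0 utility.** The trapezoidal area over 0, 0.5 and 1 year is

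0.5(u0 + u1)/2 + 0.5(u1 + u2)/2 = 0.25 u0 + 0.50 u1 + 0.25 u2.

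For caregivers, with T0 and T2 only, it is 0.50 u0 + 0.50 u2.

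**Step 2: unadjusted QALY difference with no INA effect.** If the gap at T1 and T2 is b × d:

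- Elderly: 0.25d + 0.50bd + 0.25bd = d(0.25 + 0.75b)
- Caregivers: d(0.50 + 0.50b)

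| d (assumed) | b = 0 | b = 0.5 | b = 0.7 | b = 1 |
|---|---|---|---|---|
| 0.02, elderly | 0.005 | 0.0125 | 0.0155 | 0.020 |
| 0.05, elderly | 0.0125 | 0.031 | 0.039 | 0.050 |
| 0.10, elderly | 0.025 | 0.0625 | 0.0775 | 0.100 |
| 0.05, caregivers | 0.025 | 0.0375 | 0.0425 | 0.050 |

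So 25% to 100% of a gap passes through for the elderly, and 50% to 100% for caregivers.

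**Step 3: is a gap of 0.05 plausible?** Ignoring matching, the standard error of the T0 difference is SD × √(1/90 + 1/180). With an assumed SD of 0.20 it is 0.0258, and 1.96 SE = 0.051. With SD 0.30 it is 0.0387, and 1.96 SE = 0.076. Chance alone could give about 0.05 to 0.08. Non-random selection can add to this, and matching on TFI can reduce it.

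**Step 4: does adjustment remove it?** A simulation used 4,000 runs, 180 and 90 people, d = 0.05, b = 0.6, SD 0.25 and no true effect. The expected unadjusted difference is 0.05 × (0.25 + 0.75 × 0.6) = 0.035. The simulated mean was 0.034 unadjusted, and 0.000 after regression of QALY on group and T0 utility.

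**Step 5: what it does to the ratio (illustration only).** Assume a true gain of 0.03 QALY and an extra cost of EUR 1,000, so 1,000/0.03 = EUR 33,333 per QALY. Take d = 0.05.

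- Gap favouring INA, b = 0: 1,000/0.0425 = EUR 23,529. With b = 1: 1,000/0.080 = EUR 12,500.
- Gap against INA, b = 0: 1,000/0.0175 = EUR 57,143. With b = 1 the gain becomes 0.03 − 0.05 = −0.02, a loss.

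**The case against.** A reader might infer that the plan has chosen a raw, unadjusted QALY difference, and that baseline imbalance will therefore be counted as QALYs gained or lost. The document does not support that. The Costs section names a contrast, not an estimator, and an adjusted group coefficient is also a between-group difference. It does not say how QALYs are built. The multivariate line in the Data analysis section does cover the cost-effectiveness outcomes. Covariate lists are often left to a fuller document that is not shown. The imbalance itself is hypothetical: its size and direction are unknown. The TFI spans physical, psychological and social frailty, so matching on it should narrow a utility gap.

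All of this stands as a limit on the wording. It does not remove the point. The article goes beyond silence: it names a primary economic analysis and its outcome, in a design where matching is the only stated answer to non-randomisation and omits utility and prior care use. The multivariate line names no baseline value and does not redefine that contrast. Analysing EQ-6D at each time point would leave the QALY and cost differences in the ICER uncorrected.

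A second objection is that regression on T0 utility is not a complete cure. This is also right. If a district gap stays at d throughout while the individual carry-over is b, adjustment leaves 0.75(1 − b)d. For d = 0.05 and b = 0.5, that is 0.75 × 0.5 × 0.05 = 0.019, against 0.050 unadjusted.

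**Conclusion.** The point holds as a conditional risk. The primary cost-utility contrast is stated without adjustment for T0 utility or T0 care use, in non-randomised groups matched on three other variables. If the QALY is the usual three-point area and the difference is left unadjusted, an assumed T0 gap of 0.05 yields 0.0125 to 0.050 QALY with no INA effect. Over assumed gaps of 0.02 to 0.10, the range is 0.005 to 0.100. The sign cannot be predicted.

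These sizes rest on assumed d, b and SD, and on an inferred QALY construction. They show what the stated contrast allows, not what will happen. The point merits a change because the correction is simple and its main covariates are planned for collection at T0.

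**What to change.** Add to the Costs section:

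- **QALYs, elderly.** The primary difference is the group coefficient from a regression of 12-month QALY on group, T0 EQ-6D utility, TFI score, age and gender. State how the QALY is computed from T0, T1 and T2.
- **Costs.** Estimate the cost difference in the same way, with T0 health care utilization cost as the baseline covariate.
- **ICER.** Use these adjusted differences, and show the unadjusted ones alongside.
- **Informal caregivers.** Handle them separately, adjusting for the caregiver's own T0 utility, which has weight 0.50 in a two-point area. The text says the EQ-6D is given to caregivers, but Table 1 does not list it for them. Confirm that it is collected at T0.
- **Limit.** Say that this removes measured baseline imbalance, not all confounding between districts.

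The cost is a few sentences. For the elderly, TFI, EQ-6D and health care utilization are listed instruments with T0 collection, and age and gender are already used for matching, so no new data are needed.
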